### 2.14. Monitoring

After carrying out an exhaustive evaluation of the risks and benefits of the study, the establishment of a data monitoring committee was dismissed. This is a pilot clinical trial for the establishment of future study parameters; it has a small sample size, is not a long-term study, and has a low-complexity design [132]. In this sense, it has been established that it is a clinical trial with a low level of intervention, and it has a favorable safety profile and a very low risk of serious adverse effects. Additionally, although the parameters set to be measured are extensive, the collection and data analysis are relatively simple. However, periodic information on the clinical trial status will be communicated to the HULP Ethics Committee.

However, the stakeholders involved will meet every week through an online call to update on the clinical trial progress and any eventuality that may arise during the study. This commission is made up of the principal investigator of the study who summarizes the status of the study, raises the drawbacks, possible solutions to the problems, and supervises the proper development of the study; the study coordinator who presents the patients recruited, in follow-up, discharges, etc., and manages the consumables used; the project coordinator, who stipulates the next steps of the project (publications, communications to congresses, management of body samples); and the promoter, in charge of supplying the study products and providing the consumables material of the study.

The clinical trial medical team will oversee evaluating, reporting, and managing possible adverse events and other unintended effects. In this case, it will be the principal investigator, a physician by profession, who will make the final decision to end the clinical trial.

## 3. Materials and Equipment

### 3.1. Olfactory-Gustatory Tests

#### 3.1.1. Electrogustometry

The threshold for an electric-induced taste stimulus (taste acuity) was measured using an electrogustometer (SI-03 Model, Sensonics International, Haddon Heights, NJ, USA). The electric stimulus is applied with a monopolar electrode (a single, flat, circular stainless-steel stimulus probe) placed on the tongue between the tip and behind the *sulcus medianus linguae*. The electrogustometer produces low-amplitude stimuli of a predetermined duration (0.5 s). All patients were instructed not to eat or drink for an hour before beginning the test. First, a 30 dB (256 μA) stimulus is administered to test whether the subject is capable of recognizing electrogustometric stimuli. Once the threshold is checked, the stimulation starts at the zero-stimulus amplitude, and increasingly stronger stimuli are presented until the patient identifies the stimulus. To measure detection thresholds, the two-down one-up forced-choice single staircase procedure and a stimulus-response staircase are used. If the threshold for stimulus perception is not detected, the next higher- and lower-strength stimuli are presented to the patient. The electric threshold scores are measured at the area of the fungiform papillae on both sides of the tongue. Thresholds are measured in a randomized sequence chosen by the researcher.

The test starts with the 0 dB (8 μA) configuration. If the patient fails to identify the stimulus (−) or (+ −), the intensity is increased (6 dB); if the patient succeeds in both measurements (+ +), the intensity is lowered (−6 dB). The same procedure is repeated at the new intensity, and the same criterion is maintained. If the patient fails (−) or (+ −), the intensity is increased, and if they succeed (+ +), the intensity is lowered. When the first negative point is reached, it is taken as a reference to start the analyses. From this point on, a total of 4 points need to be acquired: one positive (+ +), one negative (−) or (+ −), another positive (+ +), and another negative (−) or (+ −). This is represented in the template as a staircase. Once these four points have been obtained, an average of the decibel (dB) values obtained should be taken.

According to the guidelines of the German Society for Olfactology and Gustology, threshold differences between the left and right sides greater than 7 dB are considered abnormal [133].

#### 3.1.2. Taste Strips Test

Taste strip tests are used to measure chemical taste perception. Based on taste-impregnated filter paper strips, the taste strip test is a validated examination method to determine the ability to taste [30,134] (“Taste Strips”, Burghart Messtechnik GmbH, Holm, Germany). Four different taste strips (sweet, sour, salty, and bitter) in four different concentrations (sweet: 0.4, 0.2, 0.1, 0.05 g/mL sucrose; sour: 0.3, 0.165, 0.09, 0.05 g/mL citric acid; salty: 0.25, 0.1, 0.04, 0.016 g/mL sodium chloride; bitter: 0.006, 0.0024, 0.0009, 0.0004 g/mL quinine hydrochloride) are used. These taste strips are presented successively to the cancer patients in a pseudorandomized manner (Test sequence I: U-D-P-L-H-U-G-C-O-K-V-F-B-J-N-A-E-I-M; Test sequence II: U-H-L-P-D-U-K-O-C-G-V-N-B-F-J-E-M-I-A). Umami is not tested as a descriptor because it is not widely used in Spain. In addition to the impregnated strips, strips with no taste (blank U+V) are offered at the beginning of the test.

One hour before testing, subjects are asked not to eat or drink anything except water, not to smoke, and not to brush their teeth. For the assessment of whole-mouth gustatory function, the strips are placed on the tongue, and the mouth is closed for 10 s (the tongue may be moved). Once the strip is removed, the participant is asked to identify the taste. When a taste is not identified, participants are forced to guess. After each strip, the patient’s mount is rinsed with water to cleanse the palate.

Each correct answer yields one point with a maximum score of 16 points (4 concentrations of each of the 4 basic taste qualities). Blanks are not counted during the evaluation. At a score below the threshold value of nine, hypogeusia can be assumed regardless of age. Complete ageusia can be assumed if the highest concentrations of all four qualities are not detected. The total taste performance and the performance of each taste quality can be evaluated separately, for example, hypogeusia (total score = 7) with partial ageusia for sweet (“no perception of sweet”).

#### 3.1.3. Sniffin’ Sticks Smell Test

Orthonasal olfactory function (smell perception) is measured by the “Sniffin’ Sticks” test [135], which is based on odor-containing felt-tip pens (“Sniffin’ sticks” Burghart Messtechnik GmbH, Germany). This test consists of a total of 16 odors that are presented to the patient to be identified. The patient will not consume food, drinks, or cigarettes 15 min before testing, and tap water is permitted. For each odor pen, a choice card with 4 choices is provided (e.g., orange, strawberry, blackberry, pineapple). Patients have to choose the term that best matches their olfactory perception. Each is uncovered and held 2 cm from the tip of the nose for 3–4 timed seconds. When an odor is not identified, participants are forced to guess. The 16 pens are presented to the patient one after another at an interval of approximately 30 s. The score sums up all correct answers. Test results are used to differentiate between normosmia and hyposmia depending on the age of the patient (Figure 4).

### 3.2. Malnutrition Criteria

The nutritional diagnosis of malnutrition is established through the GLIM criteria (Global Leadership Initiative in Malnutrition), which classify nutritional status based on phenotypic and etiological criteria [23] (Table 2).

Reduced muscle mass is a phenotypic criterion with strong evidence to support its inclusion in the GLIM consensus criteria. GLIM refers to recommendations from the European Working Group on Sarcopenia in Older People (EWGSOP) [60]. Bioelectrical impedance analysis (BIA) and the body composition method are used to evaluate reduced muscle mass, and hand grip strength functional assessment is considered a supportive measure.

To assess the reduced food assimilation, gastrointestinal symptoms as supportive indicators that can impair food intake or absorption (vomiting, dysphagia, constipation, nausea, diarrhea, or abdominal pain) are considered. They are used as a form of clinical judgment to discern severity based on the degree to which intake or absorption is impaired. Symptom intensity, duration, and frequency are noted.

Inflammation status, major infection, trauma, and acute conditions associated with mild to moderate inflammation are considered. Transient inflammation of a mild degree is not considered a threshold for this etiologic criterion. Chronic disease-related is associated with malignant disease, chronic obstructive pulmonary disease, congestive heart failure, chronic renal disease, or any disease with chronic or recurrent inflammation. Indeed, C-reactive protein (CRP) is used as a supportive laboratory measure of inflammation.

The GLIM criteria require at least one phenotypic criterion and one etiologic criterion to diagnose malnutrition. Malnutrition seriousness is determined based on the phenotypic criteria classifying it as moderate or severe malnutrition [23] (Table 2).

### 3.3. Morphofunctional Studies

#### 3.3.1. Anthropometric Parameters

Anthropometric variables are taken using standard techniques, following the international norms established by the WHO [136]. Body weight is measured using a clinical digital scale (capacity 0–150 kg), preferably in the morning after 12 h of fasting and after evacuation to obtain the most stable values. When it is not possible, the time of day is noted. Height is measured with a height meter with an accuracy of 1 mm (range, 80–200 cm). This measure requires the subject to stand with their feet together and their heels, buttocks, and upper back in contact with the scale. The head should be positioned in the Frankfurt plane (the lower edge of the eye socket is in the same horizontal plane as the upper protrusion of the ear’s tragus) to obtain the highest point of the skull [137]. The patient is instructed to take and hold a deep breath, and while keeping the head in the Frankfurt plane, the measurement is taken at the end of a deep inhalation. Waist circumference is taken at the narrowest level, between the lower costal edge (10th rib) and the iliac crest. If there is no obvious minimum waist, the measurement is taken at the midpoint. The tape is readjusted to ensure that it does not slip or conform excessively to the skin. The subject should be breathing normally, and the measurement is taken at the end of an expiration (at the end of tidal volume) [138]. Body mass index (BMI) is determined using the following formula: [weight (kg)/height (m)^2^]. The relationship between the waist circumference (cm) and the height (m) of the individual is determined to obtain the waist–height index.

#### 3.3.2. Bioelectrical Impedance Analysis

Body composition is evaluated using a multifrequency BIA (Bioelectrical Impedance Analyzer), the EFG ElectroFluidGraph^®^ (Akern S.R.L., Pontassieve, Florence, Italy). Standardization of the BIA technique is a fundamental aspect of the validity of the estimates. In this study, the standard four-pole technique is used [139]. The conditions to reduce variations and guarantee the reliability of the measurement before performing the BIA are as follows: patient in a relaxed state, supine position on a nonconductive surface with bare feet and minimal clothing, limbs abducted at 45°, no metal accessories (earrings, chains, bracelets, etc.), adequate room temperature, fasting for more than 2 h and without consuming alcohol, coffee, caffeinated soft drinks or chocolate in the 24 h before the study; no strenuous exercise in the previous 24 h, preferably not being in the menstrual period, and not coinciding with the 3 days that precede the same.

Subsequently, BIA electrodes are placed on the skin’s surface, on the right hand and on the right foot, according to a standard protocol. The inductors are positioned at a distance in the metacarpal (on the back of the hand between the knuckles of the index and middle fingers) and metatarsal (top of the foot at the base of the toes) line through surface electrodes. The sensors (black clamps) are attached via electrodes to the wrist and ankle joints and therefore inside the electric field. Once placed, a low constant electrical current is passed through the electrodes. The current is at a frequency of 50 kHz and a voltage of 800 millivolts. BIA equipment measures the resistance encountered by the electrical current as it passes through the body. This resistance is then used to estimate the body composition (fat mass (kg), free fat mass (kg), body cell mass (kg), total, extracellular, and intracellular water (L), hydration (%), ASMM (kg), SMI (kg/m^2^)) and other parameters (resistance (R), reactance (Xc), impedance (Z), phase angle (PhA), and standardized PhA), taking into account the height, weight, age, and sex of the patient through a mathematical algorithm. To calculate the ASMM index, the following formula was used: ASMM (kg)/height (m)^2^.

A vectorial analysis (BIVA) of the data was carried out to determine the nutritional and hydrated status.

#### 3.3.3. Dinamometry

A dynamometer was used to measure patient strength and to determine muscle functionality in both hands. Strength was assessed by using a hand hydraulic dynamometer (Jamar^®^, Performance Health Supply Inc., Nottinghamshire, UK) with an adjustable handle, five grip positions (35–87 mm), a hydraulically sealed dual scale (pounds and kilograms), and an isometric grip force indicator (0–90 kg). The maximum force indicator remains after each reading until it is reset. The Jamar dynamometer has been shown to have high reliability and validity for measuring grip strength [140].

To ensure accurate and consistent results, the following standardized procedures are followed [141]. The patient has to rest for at least 5 min before. Any jewelry or objects that may interfere with the grip are removed. The dynamometer handle is adjusted to fit the subject’s hand size. The red peak-hold needle counterclockwise has to be zero. Patients are instructed to sit upright in an individual sitting position with their shoulder adducted and neutrally rotated, elbow flexed at 90°, wrist between 0 and 30° dorsiflexion and between 0 and 15° ulnar deviation, and forearm resting on a flat surface. The dynamometer handles parallel to the fingers. The patient is instructed to squeeze the dynamometer handle as hard as possible using their dominant hand for 5 s. The maximum force in kilograms displayed on the dynamometer is recorded. The grip strength measurement was repeated three times with a 30 s rest period between each measurement to obtain an average score. Scores within two standard deviations of the mean are considered within normal limits. For their interpretation, patient hand grip strength is compared to reference values based on age, sex, and body size for the Spanish population [62]. Grip strength is a reliable indicator of overall muscle strength and is correlated with daily living functional abilities.

#### 3.3.4. Nutritional Ultrasound

The Nutritional Ultrasound^®^ methodology is based on the technical considerations and standardization carried out in Spain [64].

Muscle ultrasound technique. Ultrasound analysis measures muscle architecture parameters [142]. The present study focuses attention on the *rectus femoris* muscle of the quadriceps due to its correlation with strength and functional execution or performance tests [65].

Grayscale ultrasonography with a linear transducer with a coefficient of variation of 1.3% is used (Mindray Z50 Serie, Shenzhen, China). The measurement of the loss of muscle thickness is carried out using a linear transducer with high-frequency sound waves (1–10 MHz). This measurement includes the *vastus medialis* and *rectus femoris* muscles.

Twenty-four hours before the start of the procedure, the patient is to avoid exercising or performing strenuous activities. The patient being tested is to wear a gown to allow easy access to the muscle. First, the patient is placed in the supine position with the legs relaxed and extended at a 45° angle. Ultrasound conductive gel is applied to the skin over the muscle. The ultrasound probe is placed on the skin and moved over the muscle to obtain the muscle tissue images. Ultrasound sends high-frequency sound waves into the muscle tissue, which bounce back to the probe and create an image on the screen. A transverse image of the right leg was obtained. With the transducer at 90 degrees to the thigh, two measurements are taken at different thigh heights. The image is taken in the lower third of the imaginary line connecting the anterior superior iliac crest and the upper border of the patella once the anterior rectus muscle is located. Data obtained by muscle ultrasound are axes (X (cm) and Y (cm)), circumference (cm), and area (cm) of the anterior rectus muscle and subcutaneous adipose tissue (cm).

The adipose ultrasound technique is useful for evaluating the fat mass compartment: subcutaneous (superficial and deep-layer) and preperitoneal visceral adipose tissue of the abdomen. With the patient in the supine position, the transducer is kept perpendicular to the skin placed between the xiphoid process and the umbilicus along the linea alba. The skin is touched as lightly as possible with the transducer so that the fat layers are not compressed. Images are taken during expiration in a transverse plane with a variable probe depth of 4–10 cm, perpendicular to the skin. Superficial and deep layers are differentiated. Visceral adipose tissue is measured using the Hamagawa technique [143]. In the transverse position, the distance between the limit of the parietal peritoneum and the linea alba on the inside at the junction of the two *rectus abdominis* muscles is measured. Data obtained by abdominal ultrasound are total adipose tissue (cm), superficial adipose tissue (cm), and preperitoneal visceral adipose tissue (cm).

The superficial subcutaneous fat layer is related to energy reserve, and a deep subcutaneous fat layer may play a role in neuroendocrine regulation via the secretion of adipokines; preperitoneal visceral adipose tissue is a visceral ectopic tissue (hepatic steatosis equivalent), and other pathological adipose tissues and visceral deposits are related to metabolic manifestations such as diabetes or atherosclerosis [44].

#### 3.3.5. Timed up and Go Test

The up-and-go test is a simple clinical assessment tool used to evaluate a patient’s ability to perform functional tasks (walking and turning), balance ability, and coordination. During the test, patients are asked to rise from a seated position (back supported and their arms resting on the armrests), walk a distance of 3 m, turn around, walk back to the chair, and sit down again. The time taken to complete the task is recorded. When the time required to complete the up-and-go test is ≥20 s, the patient is considered frail [60,68].

### 3.4. Surveys

#### 3.4.1. Taste and Smell Survey

A modified version of the Taste and Smell Survey (TSS) [144] is used to explore the prevalence, characteristics and severity of taste and smell changes since becoming ill. This TSS has been used before in the oncology setting [145,146], including advanced cancer [144]. The TSS responses generate a chemosensory complaint score. It consists of 12 items, 7 of which are related to taste and 5 related to smell. One point is awarded for each reported complaint. An additional point is awarded when it is mild/moderate or rarely/sometimes and a further 2 points if it is severe/disabling or often/always. Taste changes are scored from 0 (no change) to 10 (multiple severe changes) and smell changes from 0 (no change) to 5 (multiple severe changes). A combined chemosensory complaint score of 0 to 15 points is calculated. Two open questions (Questions 10 and 12) allow patients to describe how taste and smell disturbances impact their quality of life. Question 6 is also unscored.

#### 3.4.2. Food Daily Record

For the quantitative assessment of the intake of energy and nutrients, a daily food record is used, following the recommended guidelines [147]. Foods, drinks, dietary supplements and preparations consumed for three days (one of which must be a holiday) before the consultation are recorded. The information obtained is structured in mealtimes (breakfast, mid-morning, lunch, mid-afternoon, dinner, and other meal moments). Patients are asked about the meal place (home, work, restaurant, etc.), food consumption time, and time spent (start and end time meal is registered). Patients provide a detailed description of food consumption (ingredients, method of preparation, brands, type). Subjects are instructed to record the weight of the food consumed or, if this is not possible, to record household measurements (spoonfuls, cups, etc.). At each visit, all records are thoroughly reviewed by a nutritionist in the presence of the patient to ensure that the information collected was complete. To facilitate the process, the nutritionist uses the “Photo guide of common portion sizes of Spanish foods”, which includes 12 food groups, 204 foods commonly consumed by the Spanish population, and 944 photographs [148].

The energy and nutritional content of the foods and beverages consumed are calculated using DIAL software (Alce Ingeniería, Madrid, Spain https://www.alceingenieria.net/nutricion.htm, accessed on 1 October 2023).

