#### 2.8.5. Diet

Inadequate dietary intake is an important factor involved in the weight loss and progressive functional decline associated with advanced cancer [69]. Reduced food intake is a well-established indicator of malnutrition that has strong validity. In this sense, less than or equal to 50% of energy requirements for more than one week, any reduction for more than 2 weeks, or any chronic gastrointestinal condition that adversely impacts food assimilation or absorption is considered reduced food intake or reduced assimilation, an etiologic criterion for malnutrition diagnosis [23].

Diet is collected in the 72 h food daily record at v1, v3, v4 and v5, allowing the transformation of food consumption into energy intake, water, macronutrient intake (proteins, fats (total fat, saturated (SFAs), monounsaturated (MUFAs) and polyunsaturated fatty acids (PUFAs), carbohydrates, fiber, and micronutrient intake (vitamins and minerals)). From this information, it is possible to calculate the caloric and lipid profile as well as the coverage of the recommended intakes of the population. Obtained data are to be evaluated using the European Food Safety Authority dietary reference values [70] and the Nutritional Objectives of the Consensus Document of the Spanish Community Nutrition Society [71]. If food intake does not meet energy requirements, a high-calorie, high-protein oral nutrition supplement with fiber, EPA, DHA, beta-glucans, and enriched in L-leucine (no added sugars) will be prescribed.

Dietary habits, diversity and variety will be measured using a quantitative FFQ. To evaluate the overall dietary habits, the consumption frequency of all food items will be categorized as meeting or not meeting the criteria of the dietary guidelines for the Spanish population [72], the food pyramid for the Spanish population [73], and the nutrition goals for the Spanish population [71].

Malnourished cancer patients with taste distortion and consuming the miraculin-based food supplement are expected to improve their dietary intake from baseline (v0) to the end of the intervention (v5). The mean of the difference between intake and food frequency found between these visits will be statistically compared with those found in the rest of the treatments. The evolution of diet will also be evaluated through the different intervention visits where it will be measured (v1, v3, v4, and v5).

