#### 2.8.6. Physical Activity

Resting energy expenditure is increased in many cancer patients; however, total energy expenditure appears to be lower because of a reduction in daily physical activity [74]. In cancer patients, total energy expenditure may be estimated from standard formulas for resting energy expenditure and standard values for physical activity level [75]. To calculate the total energy expenditure and energy requirements, physical activity is evaluated. Maintenance or an increase in the physical activity level to maintain physical function, muscle mass, and metabolic pattern is a clinical practical recommendation in cancer patients [43]. Increased physical activity reduces the risk and improves survival of patients in several cancers [76].

To calculate the energy balance, the energy intake obtained in the 72 h daily food record is to be compared with the total energy expenditure calculated from the Institute of Medicine, Food and Nutrition Board [77], plus the energy derived from physical activity obtained through the International Physical Activity Questionnaire [78]. Physical activity will be evaluated at the beginning (v0) and at the end of the intervention (v5). The mean of the difference between intake and food frequency found between these visits will be statistically compared with those found in the rest of the treatments. The evolution of diet will also be evaluated through the different intervention visits where it will be measured (v1, v3, v4, and v5).

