#### 4.2.1. Visit 1 (v1)

Once it is verified that patients meet the inclusion and exclusion criteria, the experimental phase’s first visit will be made. In this visit, the patient is randomized, and the following initial measures are taken:Health study (blood pressure and heart rate);Morphofunctional assessment:
▪Anthropometric measurements;▪Electrical bioimpedance;▪Dynamometry;▪Nutritional ultrasound;▪Up and Go Test.Sniffin’ Stick Smell Test;Collection and measurement of saliva volume;Blood sample extraction coinciding with the prechemotherapy analysis:▪Biochemical parameters;▪Plasma metabolomic analysis;▪Plasma cytokine profile;▪Fatty acids from the erythrocyte membrane;▪Enzymatic antioxidant defense system in erythrocytes;▪Body oxidative stress in urine;▪Fecal microbiota and metagenome;▪Saliva microbiota and metagenome.

During this visit, the following documentation is collected:Daily Food Record (3 days per holiday);Food consumption frequency;International Physical Activity Questionnaire;Quality of life questionnaire;Feces sample;Urine sample.

Once the tests have been carried out, the patient will be instructed on the following:Nutritional treatment. If an oral nutritional supplement is needed, a polymeric, hypercaloric, and hyperproteic formula enriched in omega-3 fatty acids is prescribed depending on their energy requirements;Healthy eating guidelines for cancer patients using the book “Cooking with Science Against Cancer” as a support are given to the patient;Physical exercise guidelines.

During this visit, the study treatment (Miraculin-based food supplement or placebo) is delivered to the patient based on randomization, and the following documentation is delivered to bring the next visit (v2):Product efficacy satisfaction questionnaire (prechemotherapy);Next face-to-face visit date.

The following documentation will also be delivered to bring on the third visit (v3):Product consumption control daily sheet;Product consumption tolerance record sheet;Record sheet of adverse effects.

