#### 4.2.2. Visit 2 (v2)

Carried out 4–7 days after the chemotherapy session, during this visit, the following measurements will be made:
Anthropometric measurements;Electrogustometry;Smell and taste tests:▪Taste Strips Test;▪Sniffin ‘Sticks Smell Test.Collection and measurement of saliva volume;Taste and Smell Modified Survey;Product Efficacy Satisfaction Questionnaire (Post Chemotherapy).

The following behavioral reinforcements are also carried out on this visit:Nutritional treatment and physical activity;Consumption and registration of the assigned treatment;Tolerance and adverse effects registry.

At the end of this visit, the following documentation and material are given to the patient. These have to be delivered on the next visit (v3):Daily Food Record (3 days per holiday);International Physical Activity Questionnaire;Quality of Life Questionnaire;Blood sample extraction appointment;Feces container;Urine container.

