#### 4.2.5. Visit 5 (v5)

This visit will take place ±3 months after visit 1 (v1) and 3–4 days after the patient’s chemotherapy treatment session. This visit is similar to visit 1. A detailed version of the assessments performed is included in the Supplementary Material (File S4). 

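### The diary that measures energy intake also logs supplements, while low intake triggers a high-calorie formula; with no food-only total, a rise in intake may be formula and the arm difference may shrink

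*Protocol article*

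**What the plan says.** Section 3.4.2 makes the three-day diary the tool for quantifying energy and nutrient intake. It covers more than meals: "Foods, drinks, dietary supplements and preparations consumed for three days (one of which must be a holiday) before the consultation are recorded". The sentence on the dietary software refers only to foods and beverages, and does not say whether a prescribed drinkable formula counts as one.

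Section 2.8.5 collects the diary at v1, v3, v4 and v5 and attaches a co-intervention to low intake: "If food intake does not meet energy requirements, a high-calorie, high-protein oral nutrition supplement with fiber" is prescribed, in any arm and with no limit on when. It then states the comparison: "The mean of the difference between intake and food frequency found between these visits will be statistically compared" with the other treatments. Section 2.8.6 uses the same record for energy balance: "the energy intake obtained in the 72 h daily food record is to be compared with the total energy expenditure".

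On timing, section 4.2.1 collects the baseline diary at v1 and then says "Once the tests have been carried out, the patient will be instructed on the following". The first item in that list is nutritional treatment: "If an oral nutritional supplement is needed, a polymeric, hypercaloric, and hyperproteic formula enriched in omega-3 fatty acids is prescribed". At v2, under "The following behavioral reinforcements are also carried out on this visit", nutritional treatment is listed again. For v3, v4 and v5 the article says "This visit is similar to visit 1" and refers to Supplementary File S4, which is not at hand.

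No section defines a formula-free intake, and the covariates in section 2.13 are not named.

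**The concern.** The trial's causal story (section 2.7) is that better taste leads patients to eat more, and that this improves nutrition. The diary is the main quantitative test of the eating step. Yet low intake triggers a treatment whose energy goes into the same diary, so the measure partly records the response to poor eating.

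Two things can go wrong if formula is counted:

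1. **Within an arm.** Formula prescribed at v1 cannot be in the v1 diary but can be in the v3 to v5 diaries. The expected improvement from baseline could then appear with no change in eating.
2. **Between arms.** If prescribing responds to intake after v1, patients who eat less receive more formula. A real difference in eating is partly filled in, and total intake understates it.

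One undivided total cannot serve both planned uses. Energy balance needs formula in; the eating hypothesis needs it out. Section 2.10 says the pilot's results will help size later efficacy studies, so a diluted or formula-inflated estimate could carry forward.

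**Working it through.** The article gives no intake figure, formula dose, uptake or SD for this outcome, so there is no stated result to reproduce. Every number in steps 1 to 4 is an assumption chosen to show direction and plausible size.

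**Assumed inputs.** Energy requirement 1800 kcal. Mean food intake at follow-up 1400 kcal on placebo and 1600 kcal on active, so the true difference is 200 kcal. Baseline mean 1400 kcal in both arms; SD 400 kcal. Formula is given when food intake is below the requirement, as 400 kcal, 600 kcal or the full gap, with 50% or 80% consumed. A share d of formula energy displaces food, with d = 0 or 0.3.

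**Step 1. Mean formula energy F per arm, if re-set on current intake.** With z = (1800 − mean)/400, z is 1.0 on placebo and 0.5 on active.

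- Fixed dose: F = uptake × dose × Φ(z), with Φ(1.0) = 0.841 and Φ(0.5) = 0.691.
- Full gap: F = uptake × [(1800 − mean) Φ(z) + 400 φ(z)], with φ(1.0) = 0.242 and φ(0.5) = 0.352.

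Example, full gap at 80%: placebo 0.8 × (400 × 0.841 + 400 × 0.242) = 347; active 0.8 × (200 × 0.691 + 400 × 0.352) = 223.

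**Step 2. What each total shows.**

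- Total-intake difference = 200 − (1 − d)(F placebo − F active)
- Food-only difference = 200 + d(F placebo − F active)

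| Formula rule | F placebo / active | Total, d = 0 | Total, d = 0.3 | Food-only, d = 0.3 |
|---|---|---|---|---|
| 400 kcal, 50% | 168 / 138 | 170 | 179 | 209 |
| 600 kcal, 80% | 404 / 332 | 128 | 150 | 222 |
| Full gap, 50% | 217 / 140 | 123 | 146 | 223 |
| Full gap, 80% | 347 / 223 | 77 | 114 | 237 |

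The table uses unrounded F. Food-only at d = 0 is 200 in every row. The other two combinations (400 kcal at 80%, 600 kcal at 50%) fall inside these ranges. Total intake therefore shows 77 to 179 kcal, about 38% to 90% of the true 200. Food-only intake shows 200 to 237 kcal, 100% to about 119%, exceeding 100% only with displacement.

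**Step 3. Formula set once at v1.** It then depends only on baseline intake, so F is equal across arms in expectation. Both formulas return 200 kcal and there is no attenuation.

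**Step 4. Rise in the placebo arm with no added eating.** This is (1 − d) × F placebo. Lowest: 0.7 × 168 = 118 kcal. Highest: 404 kcal (600 kcal at 80%, d = 0). It applies under either timing, because mean baseline intake equals mean placebo intake at follow-up.

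**Step 5. A second set of assumptions.** Placebo food intake 1500 kcal, SD 400, requirement 1700 to 2100 kcal, true gain 150 or 300 kcal, full uptake, no displacement, and formula as a fixed 300 or 600 kcal or as the shortfall up to 600 kcal, again re-set on current intake. Total intake keeps 42% to 87% of the food effect. With 10 per arm, power for a 300 kcal gain is 0.39 on food only and 0.20 to 0.37 on the total.

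**The case against.** The strongest reply is that this is a matter of subtotalling a secondary variable, which an analysis plan or the full protocol may settle. The diary sentence is not wrong in itself: logging supplements is complete data capture and is what makes separation possible. The software sentence in section 3.4.2, and the references to food in section 2.8.5, lean towards food only. Total intake is a legitimate outcome for nutritional status, and food-only intake is not clean either, since formula can displace food.

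On harm, the only visit description shown that prescribes formula is v1. Reinforcing nutritional treatment at v2 is not re-prescribing, and similarity to v1 does not prove re-prescribing either. A rise common to all arms cancels in the planned comparison with placebo. Some patients may already be on oral formula at v1, since section 2.1 excludes enteral and parenteral nutrition but does not name prior oral supplements. The food frequency questionnaire keeps supplements in their own category, and a visual-analog question asks about eating more. Finally, with 10 per arm and SD 400 the standard error of a difference is 400 × √(2/10) = 179 kcal, larger than any modelled attenuation (21 to 123 kcal).

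Much of this stands: inclusion of formula is inferred, attenuation is conditional, the magnitudes are assumed, and the pilot could not resolve them. It does not remove the point. The article itself fixes the tool, the intake-triggered prescription and the comparison. If food only was meant, the energy balance in section 2.8.6 leaves out the formula; if formula is counted, the eating comparison is blurred. Either reading leaves one use badly served. Section 2.8.5 also expects improvement from baseline and follows its evolution over visits, where a formula rise does not cancel.

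**Conclusion.** The concern holds. A treatment triggered by low intake adds energy to the record that measures intake, and the article names no total that separates the two.

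- The within-arm consequence requires only that formula be counted and first prescribed at v1: about 118 to 404 kcal of apparent improvement on placebo in the assumed scenarios.
- The between-arm consequence also requires prescribing to respond to intake after v1. The article permits this but does not establish it. In that case total intake shows 77 to 179 kcal of a true 200; otherwise the difference is essentially intact.

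The direction follows from the prescribing rule; the size depends on dose, uptake and displacement figures that the article does not give. This should be corrected, with medium confidence. It concerns a secondary outcome of an exploratory pilot and leaves the electrogustometry primary outcome unaffected.

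**What to change.** From the same diaries:

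1. Use energy and protein from food and ordinary drinks, prescribed formula excluded, to test whether patients eat more.
2. Report total intake including formula beside it, for energy balance and nutritional status.
3. Report formula energy and the number of patients prescribed formula, by arm and visit.
4. State that formula may displace some food, so the two totals are read together. In the scenarios above they bracket the true difference: the total at or below it, food-only at or above it.

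The prescribing rule and patient care do not change. The cost is one extra subtotal per diary in the dietary software and one count per arm and visit, with no new data or visits.
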